## Experimental state

The study has received all approvals from the Ethics Committee to start in all participating hospitals. The study was registered on May 28, 2024 (ChiCTR2400084913). Patient enrollment started on June 1, 2024.

Timeline and Milestones:

By December 2024:

(1) Develop and finalize various SOPs.(2) Enroll eligible CHB patients.(3) Peg-IFN combined with NA therapy should be administered to both the dominant CHB population and the CHB combined with MAFLD patients.(4) Conduct regular follow-ups to monitor patient progress.

January 2025 to December 2025:

Complete the enrollment of all patients.

January 2026 to December 2026:

(1) Analyze and compare the number and function of inhibitory receptor T-lymphocytes between the two groups.(2) Assess differences in HBsAg clearance rates.(3) Compare the number and function of inhibitory receptor T-lymphocytes between HBsAg-cleared and non-cleared patients.(4) Use single-cell sequencing technology to analyze the mechanisms underlying HBsAg clearance.

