These conflicting results highlight a major gap in the current understanding of how MAFLD affects Peg-IFN therapy outcomes, particularly regarding HBsAg clearance, and underscore the need for further investigation. Our study aims to address this gap by evaluating the impact of MAFLD on the response to Peg-IFN treatment in chronic hepatitis B patients, specifically focusing on the achievement of HBsAg clearance as a marker of clinical cure. Additionally, the impact of hepatic steatosis on the immune status of CHB patients, such as T-lymphocyte function, has not been previously reported, and it remains unclear whether MAFLD affects clinical cure by influencing the immune status of the body.

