### Sample size

Since there are no existing literature reports on Peg-IFN treatment for combined MAFLD in the CHB-advantaged population, the sample size for this study is based on the results of our team’s previous research. In that study, Peg-IFN treatment of CHB and CHB combined with MAFLD patients for 48 weeks resulted in HBsAg clearance rates of 35 and 60%, respectively. Given the lack of established data in this specific population, we chose to use this estimate as it is reflective of our previous work, which involved similar patient profiles and treatment conditions. Setting the test level at *α* = 0.05 and the power of the study (1-*β*) at 0.90, the required sample size was calculated using the test module for two independent sample rates in PASS 11.0. The calculation indicated that 79 patients should be enrolled in each group. Considering a 15% dropout rate, 92 participants are needed in each group, thus expanding the sample size to 100 cases per group.

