### Methods for any additional analyses

SPSS 27.0 statistical software was used for data analysis. Categorical variables were expressed as counts and percentages, while continuous variables were expressed as mean and standard deviation. Clinical data were statistically analyzed using the Kruskal-Wallis test. Variance homogeneity across groups was assessed for each test index. If the variance was homogeneous, the LSD method of one-way ANOVA was applied; if the variance was not homogeneous, the Kruskal-Wallis test was used for comparisons across multiple groups. For comparisons between the two groups, the Mann–Whitney *U* test was employed. Immunological data, including HBsAg levels, HBV DNA titers, and immune marker levels (e.g., T-cell responses, cytokine profiles), will be analyzed using appropriate statistical methods based on the data distribution. Descriptive statistics (mean, SD, median, and IQR) will be used to summarize the data. For longitudinal analysis of immune markers (such as HBsAg clearance and T-cell responses) over the course of treatment, mixed-effects models will be employed to account for repeated measures and correlations within subjects. If immunological data are not normally distributed, non-parametric tests such as the Mann-Whitney U test (for comparisons between two independent groups) or the Kruskal-Wallis test (for comparisons across more than two groups) will be used. Cox proportional hazards regression will be utilized to assess the relationship between immunological markers (e.g., HBsAg clearance, T-cell response) and clinical outcomes, such as sustained HBsAg seroclearance or progression to clinical cure. In addition, we will conduct correlation analyses (Spearman’s rank correlation) to explore potential associations between immune parameters (e.g., cytokine levels, T-cell counts) and clinical variables (e.g., liver function, ALT/AST levels). A *p*-value of <0.05 was considered statistically significant.

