T lymphocytes play a crucial role in the progression of HBV disease, including viral clearance, the development of hepatitis, cirrhosis, and hepatocellular carcinoma, as well as in response to antiviral therapy. CD8+ T cells are particularly important, as they can induce apoptosis in virus-infected hepatocytes. Additionally, they inhibit HBV gene expression and replication in hepatocytes through a non-cytolytic mechanism by secreting IFN-*γ*. This dual function of CD8+ T cells—mediating apoptosis and inhibiting viral replication—highlights their essential role in controlling HBV infection. When HBV infection becomes chronic, T cells gradually become dysfunctional and lose their immune efficacy as the infection progresses and antigen exposure continues. This dysfunction is characterized by a decrease in the secretion of cytotoxic factors, such as IL-2, IFN-γ, and TNF (26, 27), and an increase in the secretion of immunosuppressive factors like IL-10 and transforming growth factor-beta (TGF-*β*). Additionally, there is increased expression of inhibitory receptors such as programmed death protein 1 (PD-1), cytotoxic T-lymphocyte-associated antigen-4 (CTLA-4), and T-cell immunoglobulin and mucin structural domain-3 (Tim-3) (28, 29). Inhibitory receptors are likely the primary reason for the loss of T-lymphocyte function, leading to the body’s inability to effectively clear HBV (30). A therapeutic strategy that rescues functionally exhausted T cells by blocking inhibitory receptor signaling pathways, thereby enhancing the immune response, could integrate immunotherapy with antiviral therapy. This approach holds promise as a reliable option for patients with chronic HBV infection to achieve a functional cure.

Recent studies have reported that hepatic CD8+ T cells in MAFLD mice may play a role in alleviating hepatic inflammation and fibrosis (31). Additionally, the number of peripheral blood Th1 cells in patients with MAFLD is significantly higher than in healthy individuals, leading to the hypothesis that Th1 cells may have a pro-inflammatory role (32). However, the state of T-lymphocyte immunocompetence in patients with CHB combined with MAFLD has not yet been reported.

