Based on a cohort of CHB or CHB-combined MAFLD patients receiving Peg-IFN antiviral therapy, along with a comprehensive clinical database and specimen bank, this study aims to investigate the number and function of T lymphocytes expressing inhibitory receptors in the peripheral blood of HBsAg-cleared and non-cleared patients at various time points, both at baseline and during treatment, using flow cytometry. The goal is to characterize the T-lymphocytes in patients with CHB combined with MAFLD, clarify the role of T lymphocytes expressing inhibitory receptors in HBsAg clearance, explore potential therapeutic targets, and provide insights for the development of new drugs aimed at achieving a clinical cure for hepatitis B.

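### The T-cell comparison of HBsAg-cleared with non-cleared patients is described without stratification or adjustment for MAFLD, so part of any MAFLD effect on T cells can appear as an association with clearance

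*Protocol article*

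**What the plan says.** All references are to the protocol article.

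- **The comparison.** The Experimental state section lists, for 2026: "Compare the number and function of inhibitory receptor T-lymphocytes between HBsAg-cleared and non-cleared patients". Objectives, Trial design and the Discussion describe the same contrast. The T-cell comparison between the two cohorts is a separate item in the same list.
- **The patients.** The Discussion introduces the flow-cytometry work with the words "Based on a cohort of CHB or CHB-combined MAFLD patients receiving Peg-IFN antiviral therapy", so both cohorts feed it.
- **The test.** Methods for any additional analyses assigns Mann-Whitney U under "For comparisons between the two groups", and names it again for immunological data that are not normally distributed. The section also plans mixed-effects models for markers over time and Cox regression of outcomes on markers, with no covariates named for either. Spearman correlations are planned "to explore potential associations between immune parameters (e.g., cytokine levels, T-cell counts) and clinical variables", ALT/AST among them.
- **The role of MAFLD.** Sample size takes as its basis that earlier treatment of CHB and of CHB with MAFLD "resulted in HBsAg clearance rates of 35 and 60%, respectively". Background and rationale says "it remains unclear whether MAFLD affects clinical cure by influencing the immune status of the body".
- **Adjustment.** The limitations at the end of the Discussion give age, gender and baseline liver function as examples of confounders to be controlled. MAFLD is not among the examples.

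**The concern.** The plan expects MAFLD to be related to clearance and asks whether it also alters immune status. If both are true, and MAFLD reaches clearance at least partly by routes other than the measured marker, MAFLD is a common cause of marker and outcome. A comparison of cleared with non-cleared patients that ignores MAFLD then mixes two things: a link between T cells and clearance, and the different MAFLD make-up of the two sets of patients. Sampling at baseline does not remove this, because MAFLD is already present then.

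At stake is the stated aim of clarifying the part that inhibitory-receptor T cells play in clearance. A difference could be reported with no such link inside either cohort, and a real link of opposite sign could be masked. The correlations with ALT/AST are exposed in the same way if MAFLD shifts both variables. The abstract says only that MAFLD may influence the assessment of transaminase levels.

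**Working it through.** **1. The plan's own figure.** Sample size gives 35% v 60%, alpha "0.05 and the power of the study" 0.90, and 79 per group. Two-sided, unpooled variance:

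n = (p1q1 + p2q2)(z0.975 + z0.90)² / (p1 − p2)² = (0.2275 + 0.2400)(1.960 + 1.282)² / 0.25² = 78.6, so 79.

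The figure reproduces, and the 35% and 60% are the rates the plan works from.

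**2. MAFLD share by clearance status, 100 per cohort.**
- Cleared: 35 CHB + 60 MAFLD = 95; MAFLD share 60/95 = 63.2%.
- Not cleared: 65 CHB + 40 MAFLD = 105; MAFLD share 40/105 = 38.1%.
- Imbalance: 63.2 − 38.1 = 25.1 percentage points.

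**3. Carry-over.** Suppose MAFLD shifts a marker by d SD and the marker is unrelated to clearance inside each cohort. The expected difference between cleared and non-cleared patients is (0.632 − 0.381) × d = 0.251d SD, about a quarter of the shift.

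**4. False-positive rate.** Simulation of 3,000 studies per setting: normal marker with unit SD, shift d in MAFLD, clearance drawn at 35% or 60% independently of the marker within cohort. The unstratified Mann-Whitney test is compared with a rank test stratified by MAFLD (ranks within cohort, rank-sum deviations divided by n + 1 and summed, referred to the normal), both at 5%. The article gives no value for d, so a range is shown.

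| d (assumed) | Carry-over, SD | Unstratified, 100 per cohort | Unstratified, 79 per cohort | Stratified, 100 per cohort |
|---|---|---|---|---|
| 0 | 0 | 4.6% | 5.1% | 5.0% |
| 0.2 | 0.05 | 7.0% | 5.7% | 4.7% |
| 0.5 | 0.13 | 14.0% | 12.0% | 5.2% |
| 0.8 | 0.20 | 26.3% | 21.9% | 5.3% |
| 1.0 | 0.25 | 36.1% | 28.0% | 4.9% |

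Repeat runs at 100 per cohort gave 12–14% at 0.5 SD, 25–26% at 0.8 SD and 36–37% at 1 SD.

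**5. Dependence on the clearance rates.** With 35% clearance in both cohorts the imbalance is zero and the unstratified test stays at about 5% for every d. With the rates exchanged between cohorts the carry-over changes sign and the rejection rates are much the same (13.4%, 26.3% and 36.2% at 0.5, 0.8 and 1.0 SD, 100 per cohort).

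**6. Spearman correlations.** If MAFLD shifts both variables by d and they are unrelated within cohort, the correlation induced across equal cohorts is about 0.25d² / (1 + 0.25d²). At an assumed d = 0.8 this is 0.16/1.16 = 0.138. With n = 200, atanh(0.138) × √197 = 1.95, so such a correlation would be significant about half the time.

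**The case against.** The strongest reply is that the article never calls this comparison pooled or unadjusted. The milestone is one line in a timeline and names no test. Joining it to Mann-Whitney U is an inference, and the strata of an exploratory analysis are often left to an analysis plan. The mixed-effects and Cox models could carry a MAFLD term, and the confounder list is only illustrative. Objectives also links this work to T cells in CHB with MAFLD, so contrasts within that cohort are conceivable, and there the problem disappears.

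Much of this stands. A reader might infer that the plan commits to ignoring MAFLD throughout. It does not: the covariates of the models are unspecified, not stated to leave MAFLD out. What remains is that the article does name both source cohorts, the contrast and a two-group test without covariates, and nothing in it brings MAFLD in.

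A second reply is causal. If MAFLD acts on clearance only through the measured T cells, the unadjusted association reflects a true T-cell role. That is right, and step 4 covers only the case of no link within cohort. But under that alternative the link also exists inside each cohort, so a stratified test still looks for it.

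A third reply is that evidence for a MAFLD effect on these cells is thin. The Discussion's statement that "the number of peripheral blood Th1 cells in patients with MAFLD is significantly higher than in healthy individuals" compares with healthy people and a different cell type, and the Discussion adds that T-cell competence in CHB with MAFLD is unreported. This also stands, which is why the shifts are assumptions. The correlations are openly exploratory.

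**Conclusion.** The point holds as a limited one. As described, the comparison can be confounded by MAFLD, and the test named cannot correct for it. The 63% v 38% split follows from the plan's own rates. The inflation of the 5% error rate to about 7%, 12–14% and 36% rests on assumed shifts of 0.2, 0.5 and 1 SD, on no link between marker and clearance within cohort, and on clearance differing as planned.

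A reader might go further and conclude that any MAFLD effect on T cells would be reported as a role in clearance. The figures do not support that: only about a quarter of the shift carries over, most simulated studies show no significant difference even at 1 SD, and nothing carries over if clearance is equal in the two cohorts. The comparison of clearance between cohorts, which is the primary question, is not touched.

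**What to change.** In Methods for any additional analyses, and in the cleared versus non-cleared item of the 2026 milestones:

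- Use a rank test stratified by MAFLD cohort (van Elteren) for the T-cell comparison.
- Include MAFLD as a covariate in the mixed-effects and Cox models of immune markers.
- Compute the Spearman correlations within each cohort, or as partial correlations given MAFLD.

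MAFLD status defines the cohorts, so it is known for every patient. The cost is a few lines of analysis text, with no new data, visits or patients: a free improvement. A mediation model for the question raised in Background and rationale is optional, would bring its own assumptions, and is not part of this fix.
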